### Monitoring visits

A local project coordinator will do weekly follow-ups and visits with each of the five clinical practice sites to ensure effective implementation of the individual implementation plans. The objective of the monitoring visits is to support and enhance the implementation of person-centred care and simulation-based learning at the clinical sites by ensuring management approval, providing continuous support to facilitators, and maintaining effective communication throughout the project. The local project coordinator will work as an external facilitator while the trained facilitators based at each clinical practice site will work as internal facilitators. Internal facilitators are identified as facilitators working in the implementation site [18] and the external facilitator refers to facilitation that comes from a change agency outside of the implementation site [35].

### Data collection

Both qualitative and quantitative data will be collected through a multi-faceted approach encompassing focus group interviews, key informant interviews, and register data. Focus group interviews will be used to retrieve a full picture and diversity of the participants agreeing and disagreeing with different sentiments. A few individual interviews will be conducted when there is a need for more in-depth information. Study participants will include trainers for person-centred care (*n* = 2), trained facilitators in person-centred care (*n* = 30), trained facilitators in simulation-based learning (*n* = 12), clinical preceptors (*n* = 50), and midwifery students (*n* = 30).

To capture feasibility, clarity, usability, and relevance [31] of the intervention’s profile on person-centred care, audio-recorded focus group interviews will be conducted with the workshop participants, using an interview guide with semi-structured questions. The questions concern how the training programme was perceived, the pedagogics and what the participants have gained from the course to become facilitators after the training programme. They also address the relevance of the training programme and questions related to the implementation of person-centred care.

For the intervention´s profile of simulation-based learning, focus group interviews will be held using an interview guide covering the following components of the process evaluation framework: fidelity, dose/exposure, reach, acceptability [31]. The questions concern how the course was perceived, the pedagogics, and if the participants feel ready to become facilitators after the course. For the clinical preceptors, the questions concern how the preceptors were trained by the facilitators, how the simulation material has been used in the mentoring of the midwife students, and how this has been useful when caring for patients and in supervising the midwifery students.

For the evaluation of the two profiles combined, focus group interviews will be held with the students of the first midwife program (*n* = 30), the interview guide will cover the following components of the process evaluation framework mechanisms of impact: Participants responses and interactions with the interventions, mediators, unexpected pathways and consequences [31].

To further investigate the effect of the intervention’s impact on the quality of care, particularly the influence on maternal and neonatal outcomes at the five clinical practice sites, we will collect quantitative data from the birth register, Table 1. All births for the years 2022 and 2024 will be included.

**Table 1. t0001:** Variables collected in birthregisters.

Mode of birth: Jan–Dec 2022–Jan–Dec 2024
Vaginal spontaneous birth
Caesarian birth emergency
Planned caesarian birth
Maternal mortality
Neonatal mortality
Obstetrical complications
Still births Fresh
Postpartum Hemorrhage >500 ml
Vacuum assisted birth

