### Challenges in maternal and new-born health care in the Democratic Republic of Congo

The Democratic Republic of Congo (DRC), in Central Africa, confronts challenges in maternal and newborn health, with a maternal mortality rate of 547 per 100 000 live births and newborn mortality rate of 28 per 1000 live births. These rates are among the highest in the world, despite 80% of births taking place in healthcare facilities [6,7]. Complications arising from pregnancy and childbirth are the leading causes of morbidity and mortality among women of reproductive age [7]. Escalating cesarean section rates is a concern in the DRC, as well as globally, and addressing it confronts its own set of challenges [8]. A woman’s interaction with maternity care providers significantly influences the quality of care and thus is crucial for maternal and new-born health. In resource-constrained settings, including the DRC, healthcare providers face system deficiencies that may lead to mistreatment of women and violation of human rights [9].

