### Hypothesis

Our hypothesis is that the implementation of both person-centred care and simulation-based learning in a midwifery education programme by educators will increase the quality of care in childbirth practice, and thereby improve maternal and neonatal outcomes.

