### Data analysis

Analysis of qualitative data from focus group interviews will be based on transcribed interviews, applying deductive qualitative content analysis principles [36]. The process evaluation framework will guide the analysis, emphasizing key components such as Implementation, Mechanisms of Impact, and Outcomes [31].

The maternal and neonatal outcomes will be compared between the two time periods, where Fisher’s exact test will be used for dichotomous variables and the Chi-square test for non-ordered categorical variables. The mean differences with 95% confidence intervals and p-values will be the main results in the comparative analysis. All the tests will be two-sided and conducted at the 5% significance level.

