## Impact of the research

At policy level: Through the results of this research, we hope for successful implementation of person-centred care in midwifery education and clinical practice in low-income settings. This could pave the way for policy recommendations promoting its widespread adoption across healthcare professions in the DRC and other similar contexts.At education level: We anticipate that the validated training programme ‘Mutual Meetings’ serves as a foundation and could be extended beyond midwifery to enhance healthcare education [20]. The new knowledge generated provides an opportunity for governments, researchers, and policymakers in the DRC and elsewhere to integrate person-centred care and simulation-based learning into midwifery education programmes, contributing to improved quality of care.In quality of care: If the intervention has positive effects on maternal and newborn health outcomes, such as increased proportion of vaginal birth and reduced morbidity and mortality and thus improving women’s childbirth experiences, we can through this intervention prove that equipping midwives with competence in person-centred care and simulation-based learning offers a strategic approach to improving maternal and newborn health.

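### An unadjusted 2022-versus-2024 comparison at five sites that all receive the intervention cannot carry the effectiveness conclusions drawn from it

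*Protocol article*

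**What the plan says.** The Data collection section gives the purpose of the register data as studying the intervention's effect on quality of care, "particularly the influence on maternal and neonatal outcomes at the five clinical practice sites". It then fixes the data: "All births for the years 2022 and 2024 will be included". Table 1 labels the periods "Mode of birth: Jan–Dec 2022–Jan–Dec 2024" and lists modes of birth, deaths, stillbirths and complications. It lists no maternal characteristic.

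The Data analysis section fixes the contrast: "The maternal and neonatal outcomes will be compared between the two time periods". Fisher's "exact test will be used for dichotomous variables and the Chi-square test for non-ordered categorical variables", two-sided at 5%, with differences, 95% confidence intervals and p-values as the main results. It names no comparison site, trend term, site term or covariate. The Profile sections say that both parts of the intervention go to all five sites.

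On interpretation, one specific aim is to determine the effectiveness of training facilitators. The Hypothesis is that implementation "will increase the quality of care in childbirth practice, and thereby improve maternal and neonatal outcomes". The Impact section says that, if outcomes improve, "we can through this intervention prove that equipping midwives with competence in person-centred care and simulation-based learning offers a strategic approach". It counts a higher proportion of vaginal birth among the favourable effects and mentions women's experiences of childbirth. The Background states that "Escalating cesarean section rates is a concern in the DRC".

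**The concern.** With one year before, one year after and no untreated site, the difference between the years is the sum of three things: any intervention effect, any background change over the same two years, and any change in who gives birth at these hospitals. The planned tests ask only whether that sum is zero. Larger registers do not help, because they shrink the confidence interval around a biased quantity.

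The bias can run either way. A rising caesarean trend would mask a real increase in vaginal birth or make the programme look harmful. A background decline in mortality or haemorrhage would look like benefit. The results are meant to support policy recommendations, so a wrong attribution in either direction matters.

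**Working it through.** **1. What the text allows.** The document states no number of births, site caesarean rate, effect size or power, so there is no planned figure to reproduce. The structural point needs no numbers. Let D be the expected 2024 rate minus the expected 2022 rate:

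D = intervention effect + background change + case-mix change

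Two periods at treated sites give one estimate, of D. Three unknowns cannot be recovered from it. Table 1 might be read as a continuous 2022–2024 series, but Data collection names the years 2022 and 2024, and Data analysis refers to two time periods, so 2023 is not in the comparison.

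**2. The before year.** The Setting section says the education programme started in October 2022. Three of the twelve months of the before year therefore overlap the programme. When implementation reached each site is shown in a figure not available here, so it is unknown whether site-level exposure had begun.

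**3. Illustration for caesarean birth.** Assumed, not in the documents: 30% caesarean in 2022; n = 2,500, 5,000 or 10,000 births per year over the five sites; zero intervention effect; a background rise of 1 or 2 points between 2022 and 2024. A normal approximation to the two-sided 5% test is used:

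- SE0 = √(2·p̄(1−p̄)/n), where p̄ is the mean of p1 and p2
- SE1 = √([p1(1−p1) + p2(1−p2)]/n)
- P(significant) = Φ((d − 1.96·SE0)/SE1) + Φ((−d − 1.96·SE0)/SE1), where d = p2 − p1

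Example with n = 5,000 and 30% to 32%: p̄ = 0.31, SE0 = 0.00925, SE1 = 0.00925, 1.96·SE0 = 0.01813. The first term is Φ((0.02 − 0.01813)/0.00925) = Φ(0.202) = 0.580. The second term is below 0.0001.

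| Births per year | No drift | +1 point | +2 points |
|---|---|---|---|
| 2,500 | 5% | 12% | 33% |
| 5,000 | 5% | 19% | 58% |
| 10,000 | 5% | 34% | 86% |

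Direction matters. At 2,500 births the chance of a significant result in the favourable direction is about 0.3% under a 1-point rise and 0.02% under a 2-point rise, below the nominal 2.5%; it is smaller still with more births. Nearly all the excess is apparent harm. Likewise, a true 2-point reduction against a 2-point background rise gives D = 0, so the benefit disappears.

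The result depends on the baseline too. At 5,000 births and a 2-point rise, the probability is 78% for a 15% baseline and 53% for a 40% baseline.

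**4. Illustration in the other direction.** Start from the national neonatal mortality in the Background, 28 per 1,000. Assume, with no support in the documents, a background fall of 10% per year: 28 × 0.9² = 22.7 per 1,000. Treating births as live births, the same formula gives 22%, 39% and 67% at 2,500, 5,000 and 10,000 births, almost all of it apparent benefit. A fall of 5% per year (to 25.3 per 1,000) gives 9%, 14% and 22%.

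**5. Case mix alone.** Assume a high-risk group with 60% caesarean risk against 20% for other women, growing from 25% to 30% of births. The crude rate moves from 0.25·60 + 0.75·20 = 30% to 0.30·60 + 0.70·20 = 32%. That is the +2-point column above, with no change in care.

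**6. Women's experiences.** The participants listed under Data collection are trainers, facilitators, preceptors and students. The register variables are clinical events. Nothing in the data plan records women's experiences.

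**The case against.** The strongest defence is that the study is labelled exploratory and built mainly as a process evaluation, with the register data as a further element. No sample size or confirmatory claim rests on them, and the qualitative analysis also covers outcomes. That is fair, and it is why the wording can be repaired without redesigning the study. It does not settle the matter: this is the only quantitative outcome analysis, and effectiveness language appears in the Aim and Hypothesis as well as in the Impact section.

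Three further objections stand and limit the point.

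- A reader might infer that a significant p-value will be declared proof. The documents do not support that. The sentence is conditional on positive effects, sits in the Impact section and is not a decision rule.
- A reader might infer that the caesarean trend could produce a false success. It could not: it works against the hoped-for result. A spurious benefit needs a favourable background trend, such as falling mortality, which the document does not report.
- A reader might conclude that adding 2023 and fitting a segmented regression over 36 months would settle the causal question. The documents do not support that either. If October 2022 is the start, only nine months precede it, and the site dates are not available here. Maternal deaths are too few: at the national 547 per 100,000 and an assumed 5,000 births, 5,000 × 0.00547 ≈ 27 deaths per year, or 27.35/60 ≈ 0.46 per site-month.

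The document also does not say whether other case-mix fields exist in the registers, so adjustment may not be possible.

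**Conclusion.** The point holds for the causal conclusion. As written, the outcome analysis estimates a crude change between 2022 and 2024 at treated sites, and that change cannot be attributed to the intervention. This follows from the stated years, sites, variables and tests, and needs no assumed number. The exploratory label does not cure it while the conclusions are worded as effectiveness.

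The size is illustrative. With a 30% baseline, 2,500 to 10,000 births per year and no effect, a caesarean drift of 1 to 2 points raises the chance of a significant difference from 5% to about 12% to 86%, in the unfavourable direction. The true drift, baseline and volumes at these hospitals are unknown. The statement on women's childbirth experiences has no data behind it.

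**What to change.** 1. **Wording.** In the analysis and the Impact section, describe the 2022–2024 difference as an association and not as proof of effectiveness. Remove women's childbirth experiences from the conclusion. This costs nothing.

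2. **Trend and site.** Keep month of birth and site for every record. Extract 2023, and earlier years where available, from the same registers. Report site-stratified estimates. Show the monthly or quarterly course of the common outcomes (mode of birth, postpartum haemorrhage) against each site's actual implementation date. Use segmented regression only if there are enough pre-implementation months, and report maternal deaths descriptively.

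3. **Case mix.** Adjust for maternal characteristics only where the registers record them, and state which were available.

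The cost is more register extraction (2023 alone adds one year to the two planned, about 50% more records if volumes are similar) and wider intervals than the crude contrast gives. No new participants are needed. Even with these changes, the absence of untreated sites should be stated as a limitation.

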## Methods

### Research design

The evaluation of the implementation of both person-centred care and simulation-based learning in a midwifery education programme will initially be conducted separately. Subsequently, a combined evaluation will be carried out. The implementation of the two profiles was conducted in four phases (Figure 1). This evaluation process will utilize an exploratory design guided by the principles of an evaluation framework (Figure 2). This includes a description of the implementing process, and what is delivered (fidelity, dose, adaptions, and reach), the mechanisms of impact that influence the learning (responses, mediators, unexpected pathways, and consequences) [31], and the mother and child outcomes and adherence to the created implementation plans. Ethical approval has been attained by the National Ethical Committee in Sweden Dnr: 2023–07343–01 and the National Ethical Committee of Public Health in the South Kivu Province Register number: CNES 001/DPSK/219PP/2024 and CNES 035/DPSK/219PP/2022.

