### Setting

The Evangelical University in Africa is situated in Bukavu in eastern DRC. In October 2022, a 90 credits midwife education programme started at the faculty of Medicine and Community Health for nurses, having a 3-year education on university level. The programme is at the bachelor level and adheres to the national curriculum. However, it is further innovatively designed with a profile of person-centred care and the integrated use of simulation-based learning pedagogy and materials. The clinical practice sites are situated at five hospitals located in the South and North Kivu provinces in eastern DRC.

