**Figure 3. f0003:**
[figure not shown]
Overview of the person-centred care training programme - mutual meetings.

The implementation of person-centred care using the strategy of training facilitators to support the implementation includes the following steps:
Translate the Swedish version of ‘MedMänniska’ into French.The French version of ‘Mutual Meetings’ will next be translated into French and independently be reviewed and culturally adapted by two native Congolese with knowledge and experience in healthcare in the DRC.‘Mutual Meetings-French’ will be tested by its feasibility at a three-day workshop with 30 participants including educators at the university, leaders and staff at the clinical practice sites, provincial healthcare leaders and representatives for the social community. They will also attend a follow-up workshop where a training of the final version of the Translated cultural adapted Mutual Meetings will lead to the participants becoming facilitators.After validation, person – centered care will be implemented in the five targeted clinical sites through ‘Mutual Meetings-French’ facilitators.

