### Profile simulation-based learning

Theoretical knowledge, simulation-based learning, and practical clinical training will be integrated in the midwifery education programme at both campus and clinical practice sites. As part of this simulation-based education at clinical practice, selected gynecologists and midwives will be trained to become facilitators. This study concerns implementation of three selected simulation-based learning courses: i) Essential Care for Labor and Birth (ECLB), ii) Vacuum Assisted Birth (VAB) and iii) Bleeding After Birth Complete (BABC).

The implementation strategies include the following steps:
Facilitators (*n* = 12) from each clinical site (*n* = 5) will be trained in the courses ELCB, VAB, and BABC during a 4-day facilitator training and will after completion of the courses train their colleagues at their respective maternity units (*n* = 50). The training will use the low-dose, high-frequency approach. In total, about 50 healthcare providers will be capacitated to function as preceptors for midwife students, using the ELCB, VAB, and BABC courses.The maternity care units (*n* = 5) will each receive necessary pedagogic tools related to the ECLB-, VAB-, and BABC courses including posters, flipcharts, and facilitator guides for each course as well as birth simulator mannequins and vacuum extractors.The clinical preceptors will subsequently train the midwifery students, using the low-dose, high-frequency approach aiming for weekly trainings in clinical setting through simulation-based training by utilizing the education material and mannequins provided in the ELCB, VAB and BABC courses. The person-centred care approach will be included in the simulation-based learning scenarios.

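### The 2022-versus-2024 comparison is not tied to when the intervention reached the five sites, so 2024 may count unexposed births as exposed

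*Protocol article*

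**What the plan says.** Data collection states the inclusion rule for the register data: "All births for the years 2022 and 2024 will be included". Table 1 gives the windows as "Mode of birth: Jan–Dec 2022–Jan–Dec 2024". Data analysis then compares the two periods with two-sided tests at the 5% level. Calendar year is thus the only definition of exposure in the article.

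On when the sites were exposed, the article says three things.

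- Research design, past tense: "The implementation of the two profiles was conducted in four phases". It refers to Figure 1 for the phases.
- Profile simulation-based learning, future tense: facilitators "will be trained in the courses ELCB, VAB, and BABC during a 4-day facilitator training". They then train about 50 colleagues as preceptors, who in turn train the students. The Abstract also puts facilitator training in the future.
- Profile person-centred care, future tense: "After validation, person – centered care will be implemented in the five targeted clinical sites". This follows translation, cultural adaptation and two workshops.

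None of these site steps is dated in the text. The one dated step is at the university: "In October 2022, a 90 credits midwife education programme started at the faculty of Medicine and Community Health" (Setting). The article was published on 25 June 2024, and the study was registered retrospectively on 23 February 2024.

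**The concern.** The Hypothesis section links better maternal and neonatal outcomes to implementation of both profiles. According to the Intervention section, the profiles enter clinical practice through trained site facilitators. The relevant contrast is therefore between births before and births after that training took hold at each hospital.

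The stated windows isolate that contrast only if all five sites were unexposed throughout 2022 and fully live by 1 January 2024. The article states neither, and on the second condition its sections conflict. If go-live fell inside 2024, the all-births rule places births under unchanged care in the after group. The estimated difference is then an average over exposed and unexposed births, smaller than the effect the hypothesis describes, and power falls with it. A weak or null register result would be hard to interpret without the site dates.

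**Working it through.** The article gives no number of births, effect size or power for the register comparison, so there is no figure to reproduce. The check is how much of a true effect the calendar-year contrast would retain under different start dates.

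**Inputs from the article:** windows January–December 2022 and 2024 (Table 1); programme start October 2022 (Setting); registration on 23 February 2024; publication on 25 June 2024; two-sided 5% level (Data analysis); national newborn mortality of 28 per 1000 live births (Background).

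**Assumptions:** births are spread evenly over the year; the effect starts in full on one date at all sites; the true reduction in newborn mortality is 30%, with the national rate standing in for the sites. The 2024 start dates are placeholders. Neither registration nor publication is a training date.

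**Retained effect** = exposed share of 2024 births − exposed share of 2022 births.

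With 2022 unexposed:

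- Start 1 January 2024: 366/366 = 100%.
- Start 23 February 2024: 313/366 = 85.5%.
- Start 25 June 2024: 190/366 = 51.9%.

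**Births needed** for the same power rise by roughly 1/(retained effect)²: 1/0.855² = 1.37 and 1/0.519² = 3.71.

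**Illustration on newborn mortality.** Undiluted rates are 28 and 28 × 0.7 = 19.6 per 1000. The standard two-proportion formula is n = [1.96·√(2p̄(1−p̄)) + 0.842·√(p₀(1−p₀) + p₁(1−p₁))]² / (p₀−p₁)². With p₀ = 0.028, p₁ = 0.0196 and p̄ = 0.0238, it gives 5,168 births per period for 80% power. Holding 5,168 births per period:

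| Start of exposure in 2024 | Rate in 2024 (per 1000) | Power |
|---|---|---|
| 1 January | 28 − 8.4 × 1 = 19.60 | 80% |
| 23 February | 28 − 8.4 × 0.855 = 20.82 | 66% |
| 25 June | 28 − 8.4 × 0.519 = 23.64 | 29% |

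**Outer bound for the baseline query.** 1 October to 31 December is 92/365 = 25.2% of 2022. If every birth in those months were exposed, the retained effect would fall to 74.8%, 60.3% and 26.7% for the same three 2024 dates. The last figure combines site exposure in 2022 with site training only in mid-2024. The cascade the article describes makes that pairing implausible, so 26.7% is a limit and not an expectation.

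**The case against.** The case on the other side is substantial.

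- **Mixing is inferred, not shown.** A reader might conclude that exposed and unexposed births are mixed in 2024. The article does not establish this. Verb tense and a publication date are not go-live dates, and tense is unreliable here: the article also says in the future tense that simulation will be built into a programme that began in October 2022. Research design uses the past tense, and retrospective registration points to some activity before 23 February 2024. This stands, so the point is conditional.
- **October 2022 does not contaminate the baseline by itself.** A reader might infer that three of the twelve baseline months are exposed, since the programme "it is further innovatively designed with a profile of person-centred care and the integrated use of simulation-based learning pedagogy and materials". But October 2022 is the start of a university course. Births are reached through trained facilitators and preceptors, and no section places any of that at a hospital in 2022. This stands; October 2022 is a query only.
- **Dates may be in Figure 1**, which was not available for this review. That could settle the timing. It would not alter the all-births rule, which depends on no date.
- **2023 is left out** and may be meant as a transition year. The text does not say so, and the gap does not help if training ran into 2024.
- **Different start dates by site are not stated.** Monitoring visits mentions individual implementation plans, but these need not mean different dates. This stands.
- **A late start would be visible.** Fidelity, dose and reach are evaluated and the coordinator follows sites weekly, so a null result need not be uninterpretable. That is fair, but such information would not undo the dilution or restore power.
- **Whole years balance season, and finer classification can be left to a fuller plan.** The first is a real merit, and the fix below keeps it. On the second, the inclusion rule is stated in the article, so it can be judged there.

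**Conclusion.** The concern holds in conditional form. The article defines exposure by whole calendar years with no link to site implementation, and it contradicts itself on whether implementation was past or still to come in mid-2024. If any site went live during 2024, the stated rule counts unexposed births as exposed and the estimate shrinks toward zero.

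The size is unknown. With 2022 unexposed, the loss is nil if all sites were live by 1 January 2024, about 14% of the effect for a 23 February start, and about 48% for a 25 June start. These figures rest on an even spread of births and a single step effect on a common date. The power figures also assume a 30% reduction from a national rate. The article does not support saying that dilution has occurred, or that the 2022 baseline is contaminated.

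**What to change.** 1. For each of the five sites, record the date its preceptors completed the simulation courses and the date person-centred care was launched. State in advance how the two dates define go-live.
2. Make the primary register comparison by birth month relative to those dates. Births before go-live, or within a prespecified wash-in period, are not counted as exposed.
3. Where go-live fell inside 2024, extend the register window to 12 months after go-live so that calendar months match the baseline.
4. Keep all of 2022 versus all of 2024 as a sensitivity analysis.
5. Confirm that care at the sites was unchanged in October–December 2022. If that cannot be confirmed, use January–September 2022 as the baseline, compared with the same calendar months after go-live.
6. Reconcile the past tense in Research design with the future tense in the Abstract, Profile person-centred care and Profile simulation-based learning.

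The coordinator, who follows each site weekly, should be able to supply the dates. The cost is slightly more analysis work, possibly some 2025 register months, and a later read-out. If all sites were fully live before 2024, a sentence giving the dates would settle the 2024 question.

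### Fresh stillbirth and neonatal death are compared with no combined outcome, so a change in how deaths at birth are recorded could look like fewer stillbirths with no death prevented

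*Protocol article*

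**What the plan says.** The Data collection section of the protocol article says of the effect on maternal and neonatal outcomes at the five sites: "we will collect quantitative data from the birth register, Table 1". On the population it says: "All births for the years 2022 and 2024 will be included". Table 1 has one row for "Neonatal mortality" and another for "Still births Fresh". It gives no time window for neonatal death and no row that adds the two.

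The Data analysis section then states: "The maternal and neonatal outcomes will be compared between the two time periods, where Fisher’s exact test will be used for dichotomous variables". It adds: "All the tests will be two-sided and conducted at the 5% significance level". No combined newborn outcome is named, and nothing says how a fall in one row is to be read beside a rise in the other.

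Two other sections bear on this. Under Profile simulation-based learning, staff at the five maternity units are trained in three courses, one of them on essential care in labour and birth. Under Impact of the research, lower morbidity and mortality would be taken as proof that the approach improves maternal and newborn health.

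**The concern.** A baby who shows no clear sign of life at delivery may be entered as a fresh stillbirth, or as a live birth followed by death. Where that line falls depends on how signs of life are looked for and recorded. Training in birth care takes place at these sites as part of the intervention, so the exposure under study could also change how the outcome is recorded in 2024. As described, the comparison is before against after, with no concurrent control site to reveal such a shift.

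A shift would push the two results in opposite directions. Fresh stillbirth would fall and could be read as a benefit, and neonatal mortality would rise by the same count. A baby who is revived but dies later would also move from one row to the other. With separate tests at 5%, one result can cross the threshold while the other does not, and the article would support a mortality claim without saying which row decides it.

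**Working it through.** **Plan's own figure.** There is none to reproduce: the article gives no birth volume, stillbirth rate, event count or power.

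**Inputs.**
- Test: two-sided Fisher's exact test at 5% (Data analysis).
- Neonatal mortality: 28 per 1000 live births, the national rate in the Background. Values of 15 and 10 per 1000 are assumed as lower recorded rates.
- Births per year N, fresh stillbirth rate and share re-entered f: all assumed. True deaths are the same in both years.

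**Identity.** Let S be fresh stillbirths and D neonatal deaths in 2022, and let m = f × S babies be re-entered in 2024.
- Fresh stillbirths: S becomes S − m, out of N births.
- Neonatal deaths: D becomes D + m, out of N − S and then N − S + m live births.
- Sum over all births: (S − m) + (D + m) = S + D, so unchanged.

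**Main example.** N = 10,000, 20 stillbirths per 1000, f = 20%.
- S = 10,000 × 0.020 = 200 and m = 0.20 × 200 = 40.
- D = 9,800 × 0.028 = 274.
- Fresh stillbirth: 200/10,000 against 160/10,000, p = 0.038.
- Neonatal death: 274/9,800 against 314/9,840, p = 0.11.
- Sum: 474 in both years, p = 1.00.

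**Range.**

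| Births/year | Fresh stillbirths per 1000 | Neonatal deaths per 1000 live births | Share re-entered | Fresh stillbirths (p) | Neonatal deaths (p) |
|---|---|---|---|---|---|
| 2,000 | 20 | 28 | 30% | 40 to 28 (0.18) | 55 to 67 (0.31) |
| 5,000 | 20 | 28 | 20% | 100 to 80 (0.15) | 137 to 157 (0.26) |
| 5,000 | 20 | 28 | 30% | 100 to 70 (0.025) | 137 to 167 (0.091) |
| 10,000 | 10 | 28 | 20% | 100 to 80 (0.15) | 277 to 297 (0.42) |
| 10,000 | 20 | 15 | 20% | 200 to 160 (0.038) | 147 to 187 (0.031) |
| 10,000 | 20 | 10 | 20% | 200 to 160 (0.038) | 98 to 138 (0.011) |
| 15,000 | 20 | 28 | 20% | 300 to 240 (0.010) | 412 to 472 (0.048) |

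**Smallest share that makes the stillbirth fall significant**, over 30 down to 10 fresh stillbirths per 1000: 35% to 60% at 2,000 births, 22% to 38% at 5,000, 16% to 27% at 10,000, and 11% to 20% at 20,000.

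**With sampling variation** (1,500 simulated datasets per setting, 20 stillbirths and 28 neonatal deaths per 1000, 20% re-entered), a significant fall in fresh stillbirth appears in about 0.3, 0.55 and 0.7 of datasets at 5,000, 10,000 and 15,000 births. The sum rejects in 4% to 6%, close to its nominal level.

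**Limit of the sum.** All of this assumes that every re-entered baby's death is in the birth register. If none of the 40 in the main example were captured, the recorded sum would fall from 474 to 474 − 40 = 434, and the artefact would remain.

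**The case against.** The strongest reply is that nothing here is stated wrongly. Table 1 is a list of variables to collect, the study calls itself exploratory, and a full protocol or analysis plan could add a sum. The article never says that a fall in fresh stillbirth alone will count as better survival. Because both rows are collected, an offsetting rise is there to be seen. These points lower the weight of the concern. They do not remove it: the article fixes the outcomes, periods, test and level, and ties a strong conclusion to lower mortality, yet gives no rule for two rows that move in opposite directions.

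A reader might go further and infer that re-entry will occur, or that the trained staff are the people who complete the registers. The documents support neither. They do not say who makes the entries, and they describe no teaching on detecting signs of life or on newborn resuscitation. The point is a vulnerability in how the outcomes are set up, not a demonstrated bias.

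A reader might also infer that the rise in neonatal deaths would stay hidden. That holds for only part of the range. At 15 or 10 recorded neonatal deaths per 1000, the rise is at least as significant as the fall.

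**Conclusion.** The concern holds as a conditional one. Fresh stillbirth and neonatal mortality can move in opposite directions by the same count with no death prevented, and no outcome named in the article is protected against that. In the main example the fall reaches p = 0.038 while the rise stays at p = 0.11. That example rests on an assumed birth volume, stillbirth rate and re-entered share, and on a national neonatal rate that may not match what birth registers record. With fewer births or fewer stillbirths the fall may not be significant; with lower recorded neonatal mortality or more births the rise may be significant as well.

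It would be too strong to say that the sum must become the only main newborn outcome. In an exploratory study that is partly a matter of preference. What the text supports is that the sum should be reported and that the survival conclusion should depend on it. This is worth changing before the two years are compared.

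**What to change.** In the Data analysis section, add a combined outcome: fresh stillbirth or neonatal death recorded in the birth register, with all births as the denominator. Define the recording window for neonatal death and apply the same one in both years, for example before discharge. Report the combined outcome together with its two components. State that any conclusion about improved newborn survival rests on the combined outcome and not on a fall in fresh stillbirth alone. State also that the sum is protective only as far as the register captures the deaths of babies entered as live-born.

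The cost is a few sentences. Both components are already in Table 1, although the registers must be able to support the chosen window. The small downside is that the sum does not separate intrapartum from later death, which the components still show.
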